## Abstract

**Background:**

Postprandial hyperglycemia (PPH) is a common clinical problem among patients with type 1 diabetes (T1D), which is related to high glycemic index (h-GI) meals. The main problem is linked to high, sharp glycemic spikes following hypoglycemia after h-GI meal consumption. There is a lack of effective and satisfactory solutions for insulin dose adjustment to cover an h-GI meal. The goal of this research was to determine whether a Super Bolus is an effective strategy to prevent PPH and late hypoglycemia after an h-GI meal compared to a Normal Bolus.

**Methods:**

A total of 72 children aged 10–18 years with T1D for at least 1 year and treated with continuous subcutaneous insulin infusion for more than 3 months will be enrolled in a double-blind, randomized, crossover clinical trial. The participants will eat a h-GI breakfast for the two following days and receive a prandial insulin bolus in the form of a Super Bolus 1 day and a Normal Bolus the next day. The glucose level 90 min after the administration of the prandial bolus will be the primary outcome measure. The secondary endpoints will refer to the glucose levels at 30, 60, 120, 150, and 180 min postprandially, the area under the blood glucose curve within 180 min postprandially, peak glucose level and the time to peak glucose level, glycemic rise, the mean amplitude of glycemic excursions, and the number of hypoglycemia episodes.

**Discussion:**

There are still few known clinical studies on this type of bolus. A Super Bolus is defined as a 50% increase in prandial insulin dose compared to the dose calculated based on the individualized patient’s insulin-carbohydrate ratio and a simultaneous suspension of basal insulin for 2 h. Our patients reported the best experience with such a combination. A comprehensive and effective solution to this frequent clinical difficulty of PPH after an h-GI meal has not yet been found. The problem is known and important, and the presented solution is innovative and easy to apply in everyday life.

**Trial registration:**

ClinicalTrials.gov NCT04019821

## Background

Many medical reports, together with our clinical practice, indicate that postprandial hyperglycemia (PPH) is an everyday struggle for people with type 1 diabetes mellitus (T1D), even when metabolic control seems to be adequate based on HbA1c levels. However, the definition of PPH is still not clear or reproducible. The American Diabetes Association (ADA) does not differentiate post-meal norms. The National Institute for Health and Care Excellence (NICE) established post-meal norms at a level above 162 mg/dl (9 mmol/l), whereas the International Society for Pediatric and Adolescent Diabetes (ISPAD) establishes them above 180 mg/dl (10 mmol/l) [1].

The glycemic peak is a common consequence of ingesting carbohydrate-rich meals [2]. To achieve the postprandial glycemic target, carbohydrate (CHO) counting can be a crucial factor [3–6]. A single mealtime insulin dose will cover a range of CHO amounts, with the insulin dose calculated for a meal containing 60 g CHO covering 10 g variations in CHO quantity (50–70 g) [7]. Interestingly, the postprandial glycemic peak rises with increasing CHO intake in a range of 20–80 g of CHOs, but meals containing over 80 g do not cause a greater glycemic peak and instead cause prolonged hyperglycemia [8, 9]. PPH is most often preceded by high glycemic index (h-GI) meals, which causes great glycemic variability, leading to a fast hyperglycemia increase followed by the rapid decline of glucose levels [10–14]. The area under the blood glucose curve (AUC) is 20% larger after the h-GI meal containing the same amount of CHOs compared to a low glycemic index (l-GI) meal [13]. It was also proved that in T1D patients, CHO-based meals caused an increase in the blood glucose level peak within 60–90 min with variations among individuals [10, 11, 15]. PPH and rapid and large glycemic fluctuations are adverse prognostic factors and are related to the development of cardiovascular complications, enhancement of oxidative stress, retinopathy, and certain types of cancers [5, 16]. Furthermore, a correlation between poor glycemic control and negative psychological outcomes, such as depressive symptoms, has been reported in teenagers (10–16 years) [17]. Although it is indicated that patients with T1D should consume l-GI products, the recommendation is rarely followed, especially in the pediatric population [18, 19].

## Methods

### Trial design

This study was designed as a randomized, double-blind, crossover study with an allocation ratio of 1:1. The trial was registered at ClinicalTrials.gov (NCT04019821) before the inclusion of the first patient. Any important changes in the protocol are introduced.

### Study settings and participants

The participants will be recruited from the Department of Pediatric Diabetology and Pediatrics at the Pediatric Teaching Clinical Hospital, Medical University of Warsaw, Poland. In case of a low recruitment rate, the Diabetic Outpatient Clinic, Pediatric Teaching Clinical Hospital, Medical University of Warsaw, Poland, would also be a reliable source of participants. The hospital is a tertiary referral center that provides medical care for more than 1000 children with T1D. The medical staff are adequately trained and competent in conducting clinical trials. The research will be conducted in accordance with the ethical standards and the Helsinki Declaration of 1964, as revised in 2013. In case of any changes, appropriate information will be added to the protocol registry site, and the bioethics committee will be informed. The principal investigator is responsible for the preparation of the protocol and revisions, the preparation of case report forms (CRFs), data collection and completion of the CRFs, randomization, recruitment of patients, reviewing the progress of the study, and data verification. Research physicians are responsible for data collection and the completion of CRFs, randomization, and recruitment processes.

### Eligibility criteria

Inclusion criteria are children aged 10–18 years with T1D as defined in the ISPAD Guidelines 2018 [25] with a duration longer than 1 year and those who have undergone insulin pump therapy for ≥ 3 months. Patients with celiac disease, diabetes-related complications (e.g., nephropathy), and those that are obese (defined as body mass index [BMI] at or above the 95th percentile for children and teens of the same age and sex) are excluded. The presence of comorbid conditions and treatment, which could significantly affect the glycemic values in the researcher’s opinion, and those who have withdrawn their consent to participate in the study will also be excluded. Written informed consent to participate in the study must be provided by the patients’ parents (and from the patient if they are older than 16 years).

### Intervention

The intervention will involve the administration of insulin for an h-GI breakfast in the form of Super Bolus. The participants will eat a h-GI breakfast for the two following days and receive a prandial insulin bolus in the form of a Super Bolus 1 day and a Normal Bolus the next day. The h-GI breakfast consists of breakfast cereal, cornflakes with added cold milk: 50 g CHO will come from the cornflakes and 10 g of CHO from the 2% milk (200 ml). Super Bolus is defined as the 50% increase in prandial insulin dose compared with the dose calculated based on the individual patient’s insulin-carbohydrate ratio (ICR) and the simultaneous suspension of basal insulin for 2 h. The definition of Super Bolus is based on the patients’ best experiences. Normal Bolus will be defined as the prandial insulin dose calculated based on the individual’s ICR.

### Study procedure

The study procedure is listed in Table 1. Patients who meet the eligibility criteria will be asked to enter the trial during hospitalization. Patients and their parents will receive oral and written information about the study. Verbal consent will be obtained from all participants. If the caregivers agree to participate, written informed consent will be obtained from the legal caregivers and participants older than 16 years by the recruiting physician who is familiar with the study protocol. Prior to the study, the participants will be hospitalized and qualified for a run-in period, which will last approximately 1 week. During this period, the doses of insulin will be adjusted. The 9-point glucose profile will be handled by the nurses, and based on the ICR glucose values and basal insulin rate, it will be optimized by a diabetologist to meet target fasting and postprandial glycemia. After achieving the glucose targets and adjusting the meals according to the ICRs, the allocation process of the participants will be started.

**Table 1 Tab1:** Timeline of the study

Study period							
	Enrollment	Run-in	Allocation	Post-location			Close-out
Time point	0	0	0	Day1	Day 2	Day3	Day 3
**Enrollment**							
Eligibility screen	x						
Informed consent	x						
Adjusting insulin doses		x					
Allocation			x				
**Interventions**							
A new infusion set				x			
CGM application				x			
Super Bolus, Normal Bolus					x	x	
**Assessments**							
Anthropometric measurement (body weight, height, BMI)			x				
TDD, basal insulin			x				
HbA1c			x				
Blood glucose level 30, 60, 90, 120, 150, and 180 min after prandial bolus					x	x	
Occurrence of hypoglycemia					x	x	
Register records from CGM							x
AUC, peak glucose, time to peak, glycemic rise, MAGE							x

*Abbreviations*: *CGM* Continuous glucose monitoring system, *BMI* Body mass index, *TDD* Total daily dose of insulin, *AUC* Area under the blood glucose curve, *MAGE* Mean amplitude of glycemic excursion

The participants will be randomly divided into two groups: SuBo-NoBo (Super Bolus-Normal Bolus) or NoBo-SuBo (Normal Bolus-Super Bolus). The study will last for three consecutive days. On the first day, a new infusion set with the reservoir and insulin will be inserted to minimize the chance of any leakages and occlusions. Steel needle sets and soft cannulas will be used, depending on the subject’s choice. There will be no restrictions on the insertion site of the set, except for the infected and lipodystrophy areas. The continuous glucose monitoring (CGM) system that will be used will consist of an Enlite™ sensor with a MiniLink™ Transmitter and a MiniMed® Paradigm VEO™ insulin pump (Medtronic MiniMed, Northridge, CA). Proper calibration of the device must be performed. To ease glycemic excursions during the study, participants can take the last correction insulin bolus and any modifications concerning basal insulin 3 h before the meal bolus. To avoid asymptomatic nocturnal hypoglycemic episodes, glycemic control during the nights preceding the test meals will be intensified by performing additional blood glucose meter tests at 12 p.m., 3 a.m., and 5 a.m.

On the second and third days, the test meal (h-GI breakfast) will be given in the morning. The fasting self-monitoring of blood glucose (SMBG) will be performed with a Contour® Plus Link meter with a one-step calibration of CGM. If the fasting glucose value is above 130 mg/dl (> 7.2 mmol/l), the test day will be postponed until the next day. The level was established according to the ISPAD 2018 Guidelines concerning pre-meal targets [1]. Pre-meal insulin will be administered 15 min before the h-GI breakfast as a Super Bolus (group SuBo-NoBo) or Normal Bolus (group NoBo-SuBo) on the second day and the Normal Bolus (group SuBo-NoBo) or Super Bolus (group NoBo-SuBo) on the third day. A 15-min time interval preceding breakfast was established in previous studies as optimal based on the rapid-acting insulin analog onset of action [20, 21]. The participants will use rapid-acting insulin analogs (aspart, lispro, and glargine), as applied thus far. The h-GI breakfast, planned by a clinical dietician, will consist of cornflakes (50 g of CHO) and 2% milk (10 g of CHO), with a total of 60 g of CHO. The test meal contains the following: Nestle Cornflakes with a glycemic index (GI) of 81 and a glycemic load (GL) of 40.5, while 2% ultra-high temperature (UHT) milk has a GI of 27 and a GL of 2.7. The overall GI of the test meal is 72. Despite the low GI of milk, it is a problem that milk products produce high insulinemic indexes of 90–98 [26]. The GI of the food was estimated based on the International Glycemic Index Tables, using bread as a reference. The h-GI test meal (GI 84) consisting of a ham sandwich and a drink used in the study conducted by Ryan et al. resulted in significantly higher postprandial glucose excursions at all time points between 30 and 180 min compared to the low-GI meal (*p <* 0.02). The maximum difference between the postprandial glucose excursions after each test condition occurred at 60 min, and the high-GI meal was 75.6 mg/dl (4.2 mmol/l) higher than that of the low-GI meal (*p <* 0.0001) [14].

The calculation of insulin doses will be performed based on the individual’s ICR counted per 10 g of CHO. The normal bolus will be calculated as 6 × ICR, and the Super Bolus will be calculated as 150% × 6 × ICR, with the suspension of basal insulin for 2 h after the delivered prandial bolus. The CRF containing the protocol for both groups, the personal data, and the calculations concerning insulin doses will be filled in for both groups on the first day. A closed envelope with patient allocation will be attached to the CRF. In the next 2 days, patients will eat h-GI breakfast, and the bolus order will depend on the allocation group. Nurses who will not be involved in the study will administer the right type of bolus. To ensure that the study protocols will not be mixed up and remain blind, the nurse administering the premeal bolus will check the allocation in the envelope and will provide the appropriate type of bolus. The study duration per day is planned for 3 h. No additional meals, snacks, or correction boluses are allowed during this time. An observation time of 3 h is defined as an approximation of the total lasting hypoglycemic effect after a subcutaneous insulin bolus dose. The capillary blood glucose level will be measured with a Contour® Plus Link Meter at 0, 30, 60, 90, 120, 150, and 180 min after insulin administration with a continuously working monitoring system. There is a high possibility that rapid glycemic fluctuations will be observed after an h-GI meal. Therefore, the blood glucose level can be checked with both the CGM and glucometer to obtain the highest accuracy of glycemic level at the specified time point. Caregivers and patients will also be instructed to report symptoms of hypoglycemia with additional glycemia measurements. Hypoglycemia will be defined as the glucose level below or equal to 70 mg/dl (≤ 3.9 mmol/l), which is treated as a clinical hypoglycemia alert according to the ISPAD Guidelines 2018.^1^ If hypoglycemia occurs, the patient will receive 0.3 g/kg of glucose/saccharose. After 15 min, the glucose level must be controlled again. If hypoglycemia persists, the patient will receive the next dose of glucose/saccharose, until a glucose level over 70 mg/dl is achieved. The presence of hypoglycemia will not suspend the study process, and SMBG will be performed as it is established. The records from the CGM will be registered using the Medtronic Care Link Pro Software and discussed with the patients for educational purposes. The participants may discontinue the trial at any point in time without giving a reason. The researchers will make every effort to supervise, educate, and regularly control the patients to provide the proper study process.

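### The fasting start rule has an upper limit (130 mg/dl) but no lower one, so a child at or below 70 mg/dl still meets the written conditions for the full meal bolus

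*Protocol article*

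**What the plan says.** All of this is in the Study procedure section of the protocol article, in the text after Table 1.

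- **Start rule.** "If the fasting glucose value is above 130 mg/dl", the test day moves to the next day. The reason given is: "The level was established according to the ISPAD 2018 Guidelines concerning pre-meal targets". This is the only glucose condition for starting.
- **Dose.** The Normal Bolus is 6 × ICR and the Super Bolus is 150% of that with basal insulin suspended for 2 h. ICR is counted per 10 g of carbohydrate. The form is completed ahead of both mornings: "the calculations concerning insulin doses will be filled in for both groups on the first day". The insulin is given 15 min before a 60 g breakfast.
- **Hypoglycemia.** "Hypoglycemia will be defined as the glucose level below or equal to 70 mg/dl". If it occurs, "the patient will receive 0.3 g/kg of glucose/saccharose". Glucose is checked again after 15 min, and sugar is repeated until the value is over 70 mg/dl. The text adds: "The presence of hypoglycemia will not suspend the study process".
- **The night before.** "To avoid asymptomatic nocturnal hypoglycemic episodes, glycemic control during the nights preceding the test meals will be intensified", with extra meter tests, the last at 5 a.m. On insulin adjustments, "participants can take the last correction insulin bolus and any modifications concerning basal insulin 3 h before the meal bolus".

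**The concern.** The article treats fasting glucose as a condition for starting and gives it a number, a consequence and a source, but only for high values. It names 70 mg/dl as the hypoglycemia alert and credits that to the same guideline family, yet does not use it as a start condition.

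Safety is the main stake. The Harms section calls hypoglycemia the most probable harmful effect, and the participants are children aged 10–18. As the text stands, a low fasting reading neither delays nor withholds the insulin.

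Standardisation comes second. The 130 mg/dl limit is there to give comparable starting points. A low start, possibly with rescue sugar before the 90-minute reading, departs from that aim. If staff step in on their own judgement, whether they delay, reduce or postpone is left to the case. The Compliance section counts a wrong insulin dose as non-compliance and makes no exception for a protective reduction.

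**Working it through.** **1. The written rules, by fasting value**

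| Fasting SMBG (mg/dl) | Start rule | Dose due | Other text |
|---|---|---|---|
| above 130 | postpone | none that day | – |
| above 70, up to 130 | start | 6 × ICR or 9 × ICR | – |
| 70 or below | start conditions met | 6 × ICR or 9 × ICR | rescue rule, if it applies before the bolus |

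The last two rows differ only in the rescue rule. That rule follows the description of the 3 h observation period, with sampling times counted from insulin administration, so its natural place is after the bolus. There are two readings:

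- If it covers post-bolus lows only, the article gives no response to a fasting low.
- If it covers fasting lows too, the child gets sugar, a recheck at 15 min and repeats until above 70 mg/dl. Nothing makes the bolus wait for the recheck.

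The gap remains on either reading. On the second it is only a question of sequence.

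**2. Dose due**

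- Normal Bolus: 6 × ICR, nominally 6 × 10 = 60 g, with basal running.
- Super Bolus: 1.5 × 6 = 9 × ICR, nominally 9 × 10 = 90 g, before a 60 g meal, partly offset by 2 h without basal.

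No basal rates are given, so the net insulin excess cannot be computed.

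**3. Number of test mornings**

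The planned total is 72 (Sample size section). As a check on that figure: (82 × (1.960 + 0.842) / 30)² = 58.7, rounded up to 59. Then 59 / 0.8 = 73.75, or 74, and 59 × 1.2 = 70.8, or 71. So 72 is reproduced within two patients, and the present point does not depend on it.

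- All 72 complete: 72 × 2 = 144 mornings. One per cent is 1.44, of which half (0.72) are Super Bolus mornings.
- After 20% withdrawal: 0.8 × 72 = 57.6, and × 2 = 115.2 mornings. One per cent is 1.15, half of it 0.58.

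The document gives no distribution of fasting glucose and none is assumed here. These are conversion factors, not estimates of frequency.

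**4. Size of a rescue dose**

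Body weight is not given. Assuming 30 to 70 kg, 0.3 g/kg is 0.3 × 30 = 9 g to 0.3 × 70 = 21 g. Against the 60 g meal that is 9/60 = 15% to 21/60 = 35%. The fixed bolus does not allow for it.

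**5. Effect on the primary comparison**

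A fasting low precedes that morning's bolus, and bolus order is randomized, so lows should fall equally on both treatments in expectation. This assumes that the first day's bolus does not shift the next morning's fasting glucose. The Statistical analysis section also adjusts for baseline. That adjustment does not remove the effect of rescue sugar, but what is left is added noise at 90 minutes and not a shift towards either bolus.

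**The case against.** **A reader might infer that the protocol orders staff to dose a hypoglycemic child**, from the sentence "The presence of hypoglycemia will not suspend the study process". The document does not support this. The sentence follows the 3 h post-bolus window and goes on to say that meter readings continue as scheduled. It concerns continued measurement after a low and is no evidence about dosing before one. What can be said is that the written start conditions do not exclude such a child.

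**The safeguards are real.** Participants are hospitalized, a diabetologist adjusts doses to target in the run-in, there are night tests and CGM, and a physician visits every 30 min. The Compliance section foresees that the regimen may be interrupted, the Blinding section allows unblinding for the patient's management, and a DSMB reviews adverse events. This stands as a reason to expect few low starts and sensible handling. It does not close the gap, because none of these is a start criterion and the 30-min visits follow the dose.

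**An article condenses the full protocol**, and bedside handling of a pre-meal low may be set out there. This has some force. But the article does state the start rule, with threshold and consequence, and states it one-sided. A reader would take it as complete.

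**The 9 × ICR dose before 60 g does not measure the harm.** That is right. It is the intervention on every Super Bolus morning and would apply equally at 71 mg/dl. It describes what is due and does not quantify the risk from the missing limit.

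**Conclusion.** The point holds as a one-sided start rule. With fasting SMBG at or below 70 mg/dl, a child meets the written conditions for a bolus fixed on day 1, and no text makes that bolus wait for treatment and recheck. It is a minor-to-moderate matter of safety and baseline standardisation.

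Its frequency cannot be derived from the document and is probably low, given the run-in and night checks. A reader might also infer a biased primary result. With randomized order and baseline adjustment the documents do not support that.

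The conclusion assumes that no lower limit stands in the full protocol, which was not available.

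**What to change.** In Study procedure, make the rule two-sided at the protocol's own threshold. Suggested wording: *If the fasting SMBG is above 130 mg/dl, or at or below 70 mg/dl, the test day will be postponed until the next day.*

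This adds one clause and uses the postponement mechanism already in place. The cost is a few extra postponed days, at the rate worked out above (about 1.4 of 144 mornings for each 1% at or below 70 mg/dl).

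Second choice, if clinicians prefer not to lose the morning: treat and recheck under the existing rescue rule, give the bolus only once glucose is above 70 mg/dl, and record the rescue dose. This avoids postponement, but the rescue sugar stays in the measured response.

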
### End points

The following is the primary endpoint:
Capillary blood glucose level 90 min after the administration of the prandial bolus as meals with h-GI typically cause blood glucose level peak within 60–90 min in T1D patients

The following are the secondary endpoints:
Capillary blood glucose levels at 30, 60, 120, 150, and 180 min after administration of the prandial bolusThe number of hypoglycemia episodes based on SMBG

The following data are based on the CGM:
Glycemic rise (GR)—the difference between the baseline and the maximum glucose valuePeak glucose level (PG)—the maximum value of glycemia during 3 h of post-mealtimeTime to PGArea under the blood glucose curve (AUC)Mean amplitude of glycemic excursion (MAGE)—the standard deviation of blood glucose (SDBG) obtained from all blood glucose concentrations within 3 h of post-meal timeTime in the postprandial glucose range between 70 and 180 mg/dl (4.0–10.0 mmol/l)

